**5.4 Recruitment and informed consent.** New patients will be recruited on the first day of treatment in the clinic (Day 0). At the end of their initial intake procedures of their first day, patients will be asked if they are interested in hearing information about a study that is testing a novel approach to enhancing methadone treatment, for which they would receive paid compensation. The PI will contact the intake coordinator by 9:00 AM to receive a list of patients who are new intakes to the clinic and who are willing to hear about the study. Those patients who indicate their interest will be approached by the PI (or the study research assistant) later that morning as they are awaiting their methadone dosing in the waiting area of the clinic (normal waiting times vary from between 30 minutes to an hour, providing ample time for a consent and scripted recruitment). At this point, the PI will introduce herself, and will assess interest in study participation. Interested patients will be directed to a small interview room located proximal to the waiting area, and a few steps from the nurses' station. The door will be closed, and the investigator will determine whether the patient meets study eligibility criteria (I/E confirmation), and if so, will obtain informed consent and an authorization for release of Health Insurance Portability and Accountability Act (HIPAA) information for specific data related to OUD treatment. The investigator will then assess comprehension with an Evaluation to Sign Consent form (IC Evaluation). Participants will be asked to provide a suitable method of contact (phone number, e-mail, or consent to be contacted through a flag placed on the person's name in Methasoft, the electronic health record platform used at the UMATC). At the end of the baseline meeting, participants will be given an appointment reminder card with follow-up meeting dates for the 4 return visits. On the day prior to each of these meeting dates, contact will be made with the participant to remind him/her of the next scheduled appointment with the study team.

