**5.4.1 Script and study information provided.** Patients are fully debriefed of all study procedures during the informed consent process. Participants are informed that their participation in the trial will have no effect on ongoing treatment afforded by the clinic, and further, that they have the right to withdraw from the study at any time with no impact on their clinical treatment. During and following consent, the notion is reinforced to the patients that the

research study is “designed to investigate the efficacy of methadone treatment that is enhanced via inner healing processes using placebo effects.” A script will be used as a conversational guide to inform patients of the study rationale and procedures (Appendix I). This script has a positive framing and describes in lay terms the science that underlies placebo effects and pharmacological conditioning, with an aim to facilitate the placebo response in a non-deceitful manner. Following the conversational reading of the script, the investigator will ask the participant to view a video of a CBS New York News piece that describes scientific studies of the successful use of the placebo phenomenon as a therapeutic intervention for irritable bowel syndrome. The participant then completes the Day 0 (baseline) assessments. As a final step (and to ensure equal investigator/participant time), prior to treatment allocation, the investigator will give the participant a placebo pill information sheet. This handout will contain explicit instructions on how to take the pill, the pill’s formulation, and the contact information for a study team member who will be able to answer any questions that the participant may have about the placebo pill or the study.

**5.5 Randomization and treatment allocation.** Prior to study inception, random treatment allocation will be generated by an independent investigator in unequal block fashion (60:40 intervention:control). Randomization consists of sequentially numbered opaque envelopes containing treatment assignments drawn from a computer-generated random number sequence. These numbers are used to assign participants to either C-OLP or TAU. Two stacks of envelopes will be created to ensure an even distribution of men and women (N=30/group/sex for a total of 120 random treatment allocations).

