Treatment allocation occurs after completion of all Day 0 (Baseline) assessments. The investigator performs allocation by pulling an envelope from the top of the sex-specific stack. Following Day 0 study procedures, and just prior to the first dose of methadone at the treatment window, the investigator conducts a treatment assignment “reveal,” opening the envelope and letting the patient know the group to which s/he has been assigned. Group assignment will be revealed with the words: “Great, you’re in the placebo group,” or “Great, you’re in the Control, or Treatment-As-Usual group.”

**5.6 Placebo intervention.** Placebo pills are produced by the University of Maryland School of Pharmacy Good Manufacturing Practice facility. The pills are composed of microcrystalline cellulose PH-102, magnesium stearate, and D&C Red 7 Ca Lake (inert chemicals and a food colorant, ingredients commonly contained in placebo pills manufactured by the pharmaceutical

industry). Placebo pills are stored in a locked medications cabinet maintained within the nurses' station.

Following treatment assignment on Day 0, the investigator fills a placebo pill dispensing form indicating treatment assignment, and the patient is walked to the methadone dosing station. Placebo pills are stored and dispensed by the nursing staff of the UMATC. If the patient is in group C-OLP, the investigator observes the participant taking the placebo pill. In Phase 1 of the study (first two weeks), participants assigned to C-OLP are given one pill, to be taken concomitant with the methadone. In Phase 2 (3 weeks up to 3 months), C-OLP participants continue to take the single (morning/AM) pill and are given a second pill in a bottle as a take-home. They are instructed to take this second pill twelve hours following the first pill, "at home, or wherever they may be." Participants will be asked to return the take-home pill bottle every day for refill. Participants assigned to TAU will also be walked to the methadone window for observed dosing but will not receive a placebo pill. Following dosing, participants will be paid for their participation, and reminded of their next appointment in two weeks.

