**5.7 Post-baseline meetings with study team.** Following the initial (baseline, Day 0) meeting, all participants will be asked to meet with a member of the study team at the following intervals: 14-, 28-, 56-, and 84-days following intake, periods of time that roughly correspond to 2 weeks, 1-, 2- and 3-months of treatment. Participants will be paid \$25 for each 30- to 45-minute study visit, for a total possible \$125. Because study participants are clients of the UMATC, they must come to the clinic daily for the first several months of their OUD treatment, facilitating follow-up with the study team (the research study team is co-located at the UMATC).

**5.8 Blinding.** At all stages of the study, methadone dose adjustments are conducted by an independent clinician blinded to treatment allocation and to when a participant is enrolled in the study. Additionally, because treatment allocation occurs only after Day 0 (baseline) assessments are complete, study team members are blind to treatment assignment for all of Day 0 procedures. Finally, data analysts are blind to treatment allocation.

**5.9 Urine toxicology screens.** Urine drug screening will occur *via* two methods: (1) a point-of-care Quik-tox screen (11 panel; LabCorp) conducted by clinic staff, results of which are reported immediately, conducted at baseline and then at monthly (random) intervals post-baseline; (2) and liquid chromatography–tandem mass spectrometry (LC-MS/MS) testing for a panel of more than 240 drugs, including new psychoactive substances, as well as other illicit and prescription

drugs. All testing is conducted by the Division of Forensic Toxicology, Armed Forces Medical Examiner System and coordinated by the University of Maryland, College Park Center for Substance Abuse Research (CESAR) staff. Urine is collected from participants during each of the five meeting times, and the Quik-tox screen is conducted only on samples from meeting one (baseline); the LC/MS/MS testing is conducted on all samples (baseline and 2 weeks, and 1-, 2- and 3-months post-baseline screening).

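### Sections 5.5 and 5.8: the recruiting team draws and openly reveals blocked envelopes, so drawing after baseline does not by itself secure the Day 0 blind

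*Protocol*

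**What the plan says.** **Recruitment and baseline.** Section 5.4 has the PI or the research assistant approach patients on Day 0. It then says that "the investigator will determine whether the patient meets study eligibility criteria (I/E confirmation), and if so, will obtain informed consent". Section 5.4.1 places the recruitment script and a video before the baseline assessments: "This script has a positive framing and describes in lay terms the science that underlies placebo effects and pharmacological conditioning". Its stated aim is to promote the placebo response. Under 9.1 a study team member administers the assessments, and under 6.2.4 the OOWS is scored by the experimenter.

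**Allocation.** Section 5.5 says that "random treatment allocation will be generated by an independent investigator in unequal block fashion (60:40 intervention:control"). It adds: "Randomization consists of sequentially numbered opaque envelopes containing treatment assignments drawn from a computer-generated random number sequence". There are two stacks by sex, described as "N=30/group/sex for a total of 120 random treatment allocations". After baseline, "The investigator performs allocation by pulling an envelope from the top of the sex-specific stack". The same role opens the envelope and tells the patient the arm just before the first methadone dose.

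**Blind.** Section 5.8 argues that, because allocation follows baseline, "study team members are blind to treatment assignment for all of Day 0 procedures". It also has dose adjustments made by an independent clinician who is blinded to allocation and to enrolment.

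**The concern.** Concealment has two parts. The next assignment must not be readable, and it must not be inferable. Opaque numbered envelopes opened after baseline serve the first. Section 5.8 treats that timing as enough for the second, and it is not. In a blocked list whose past assignments are all known, the places left in the current block carry information about the next one. The ratio and the per-sex totals are printed in the protocol, and the people who see each reveal recruit and rate the next patient.

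Three things are exposed before the reveal:

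- **Consent.** How strongly a patient is encouraged to take part.
- **The script.** It is delivered conversationally, is meant to raise expectancy, and is given before allocation to both arms. Delivering it differently according to a guess would make it part of the difference between arms.
- **Baseline ratings.** The longitudinal model in 7.3.2 fits a single baseline mean to both arms, which is justified by concealed randomisation. Each drug-use analysis also keeps only participants who reported using that drug in the two weeks before baseline.

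Selective enrolment or uneven script delivery could reach the primary outcome. Baseline rating bears on the longitudinal outcomes only.

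**Working it through.** The protocol gives no figure for predictability, so there is none to reproduce. The question does not touch the power calculation in 7.1.

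**Inputs from the protocol.** 120 allocations in two sex stacks; ratio either 60:40 or 30 per group per sex (both in 5.5); blocked list; every past assignment revealed.

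**Assumptions.** Block length is not stated, so blocks from 2 up to a whole stack of 60 are examined. In the table the guesser has tracked all earlier reveals in that stack, knows the block length, and names the arm with more places left, splitting ties evenly.

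**Correct guesses.** With *a* C-OLP and *b* TAU places left, the chance of a correct guess is max(*a*, *b*)/(*a* + *b*). Averaging over all orders of the block gives the share correct. For a 2:2 block the four positions give 1/2, 2/3, 2/3 and 1. The sum is 2.833, and 2.833/4 = 0.708.

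**Certain assignments.** An assignment is certain once one arm is used up. The expected number per block is *a*/(*b*+1) + *b*/(*a*+1), with *a* and *b* now the block's starting counts. For 2:2 this is 2/3 + 2/3 = 1.333 of 4, or 33%. For 3:2 it is 3/3 + 2/4 = 1.5 of 5, or 30%. For one 30:30 stack it is 60/31 = 1.94 of 60, or 3%.

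**Expectation gap.** This is the probability of guessing C-OLP when the truth is C-OLP, minus the same probability when the truth is TAU. For 3:2 it is 0.867 − 0.500 = 0.367.

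| Block (C-OLP:TAU) | Correct | Chance | Certain | Certain of 120 | Gap (points) |
|---|---|---|---|---|---|
| 1:1 | 75% | 50% | 50% | 60 | 50 |
| 2:2 | 71% | 50% | 33% | 40 | 42 |
| 3:3 | 68% | 50% | 25% | 30 | 37 |
| 30:30 (one stack) | 57% | 50% | 3% | 4 | 15 |
| 3:2 | 72% | 60% | 30% | 36 | 37 |
| 6:4 | 68% | 60% | 18% | 21 | 27 |
| 12:8 | 66% | 60% | 10% | 12 | 19 |
| 36:24 (one stack) | 62.5% | 60% | 3.5% | 4 | 9.5 |

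**If block lengths vary and are unknown.** A simulated guesser who simply names the arm that is behind in the stack, at 1:1, is right 70% of the time with blocks of 2, 4 and 6 mixed, and 68% with 4, 6 and 8. Above-chance guessing therefore does not depend on knowing the block length. What is lost without that knowledge is mainly the certainty.

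**The two ratios.** 60:40 of 120 is 72 against 48. Thirty per group per sex is 60 against 60, and 7.1 also assumes 60 per group. The two statements in 5.5 cannot both describe the list.

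**The case against.** Much can be said for the protocol's procedure. The list is computer-generated before the study by someone independent. The envelopes are opaque and sequentially numbered, and the draw follows all Day 0 assessments. Not publishing the block length is good practice, and "in unequal block fashion (60:40 intervention:control") may mean that block sizes vary. Section 8.3.1 plans a procedures manual meant to reduce misassignment, which could cover envelope custody.

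Room for selection is also limited. The intake coordinator supplies the list of willing patients. Recruitment happens only on Day 0, so nobody can be held back for a preferred envelope. The exclusions in 5.3 are mostly matters of fact. The primary outcome is a charted dose, adjusted by a blinded clinician.

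All of this stands and sets the size of the point. None of it repairs the reasoning in 5.8, because timing does not stop inference from past reveals. The blinded clinician protects how the dose is set, but not who is enrolled or how the script is delivered.

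Several stronger readings are tempting but unsupported:

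- **That the team knows the next assignment.** Certainty needs knowledge of the block length as well as tracking of reveals, and the protocol documents neither.
- **That one person does every step.** Section 5.4 names the PI or the research assistant, and 9.1 any team member. The point needs only a small team that shares its reveals.
- **That the stacks lie in view of the recruiter.** The text does not say so.
- **That misrated baseline OOWS distorts the 90-day dose.** The OOWS does not enter the t-test in 7.2.
- **That the unadjusted t-test is at fault.** Covariate adjustment would not remove differential script delivery.

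**Conclusion.** The point holds as a weakness in the stated procedure and an error of reasoning in 5.8. It does not show that allocation was subverted or that the result is biased. A team that tracks reveals can guess above chance: 57% to 75% correct at 1:1 against 50%, or about 63% to 72% at 60:40 against 60%. Between about 3% and 50% of assignments would be certain for someone who also knew the block length. C-OLP would be expected about 10 to 50 percentage points more often before true C-OLP assignments than before true TAU ones.

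The low ends belong to a single block per stack, where the problem is small; the high ends belong to blocks of 2. Everything rests on the unstated block length and on the team tracking and sharing reveals. No effect in milligrams can be derived from the protocol. The change is worth making because it is cheap and the script is part of the intervention.

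**What to change.** **Section 5.5, preferred.** The independent investigator loads the list into the trial's REDCap project, stratified by sex, with randomly varied block lengths withheld from the study team. REDCap releases the assignment only after eligibility, consent and completion of the Day 0 assessments are marked there. This depends on a randomisation function being available, which the protocol does not state. Release should not wait for full entry and locking: under 7.4 and 8.1 data are captured on paper and locked only after a second observer's check, while the patient is waiting for a methadone dose.

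**Section 5.5, if envelopes are kept.** State that they are sealed and held by someone outside recruitment and assessment, and that each draw is logged. That person must be reachable at every enrolment.

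**In either case.** Take the block structure and per-stack totals out of documents the recruiters see, and reconcile 60:40 with 30 per group per sex. In 5.8, rest the Day 0 blind on this concealment, not on timing alone.

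**Cost and limits.** This takes a short amendment, the REDCap setup and one completion mark per patient before release, with no extra patients or visits. Varied blocks allow slightly more temporary imbalance between arms. They mainly remove certainty; some above-chance guessing remains wherever assignments are open, so the withheld scheme and separate custody are needed as well.

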## **6.0 OUTCOME ASSESSMENTS**

**6.1 Primary outcome.** Mean dose of methadone at 3 months (90 days) post-baseline (entry into treatment) will be recorded. These data are obtained from patient charts documenting daily records of methadone dose dispensed.

**6.2 Secondary outcome measures.** Secondary outcome measures include assessments of treatment retention, self-reported drug use, opioid withdrawal, craving, quality of life, and sleep. All measures will be obtained via facilitated self-report at all five time points, except for sleep, which will be measured only at baseline and one- and three-months post-baseline to maintain fidelity to the instrument's measure of "past-month" sleep.

**6.2.1 Treatment Retention.** Clinic attendance data will be obtained from participant Methasoft records. Three-month retention will be measured as a binomial variable (retained in treatment at the 90th day, yes/no). For descriptive purposes, retention also will be counted as the total number of days retained in treatment, starting at the participant's intake date, up to 3 months (90 days). The study team adopts the clinic's definition of discharge: 30 continuous days of treatment absence. For participants who are not retained in treatment at the 90th day, the last visit to the clinic prior to their discharge will be logged as the final day in treatment.

**6.2.2 Self-reported Drug Use.** Drug use is assessed via self-report of past-two-week use of four common substances: opiates (including heroin, fentanyl, and non-prescribed opioid use), cocaine, benzodiazepines, alcohol, and a fifth broad category of "other." The total number of days used (out of a total possible 14) will be recorded.

**6.2.3 Subjective Opiate Withdrawal Scale (SOWS).** The SOWS is a 16-item self-administered rank assessment of the severity of acute symptoms of opiate withdrawal, with anchor scores of 0 and 4 corresponding respectively to "not at all" and "extremely," for a possible total score of 64.

**6.2.4 Objective Opiate Withdrawal Scale (OOWS).** The OOWS is a 13-item experimenter-administered assessment of objective symptoms of opiate withdrawal (e.g., yawning, perspiration); symptom presence is scored a “1” for a possible total score of 13.

**6.2.5 Craving.** Participants will rate their craving for drugs using a one-item craving visual-analog scale adapted from MacKillop and Lisman (2008) and Jobes et al (2015), using the wording: “Please rate how intensely you want to use drugs right now; 0 = “I don’t want to use drugs at all,” and 100 = “I really want to use drugs.” The single-item VAS generates especially robust and reliable results, perhaps on account of its minimal response burden (Jobes et al., 2015) and minimization of test-retest effects.

**6.2.6 Abbreviated World Health Organization Quality of Life Assessment (WHOQOL-BREF).** The WHOQOL-BREF is a 26-item cross-cultural quality of life profile with scores that measure the following broad domains: physical health, psychological health, social relationships, and environment. The WHOQOL-BREF is a shorter version of the original instrument and is better suited for use in large research studies or clinical trials, and has been used previously in the opioid use disorder context and particularly, in this clinic.

**6.2.7 Sleep quality.** Sleep quality will be assessed using the Pittsburgh Sleep Quality Index (PSQI), a 19-item questionnaire to assess past-month sleep quality and disturbances. The 19 self-rated items are combined to form 7 “component” scores, each of which has a range of 0-3 points. In all cases, a score of “0” indicates no difficulty, while a score of “3” indicates severe difficulty. The 7 component scores are then added to a global score, with a range of 0-21 points.

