#### **4.0 CLINICAL OUD DIAGNOSIS AND TREATMENT**

Methadone is dispensed daily Monday through Saturday with a take-home dose given for Sunday. All patients admitted to the methadone program are assessed by a nurse practitioner and a board-certified addiction medicine physician and are initiated on a standard protocol for treatment of OUD with methadone. Initial methadone doses are individualized with a typical starting dose of 25-30 mg/day that is increased by 5 mg every other day to a targeted holding dose (~80-120 mg). All dose increases are discussed with the treatment team and approved by the OTP's medical director. Patient dosing encounters are logged in the clinic's electronic health record management platform (Methasoft, Netalytics, Greer, NC) and can be accessed for information relevant to treatment retention. Per standard clinic operating procedures, and in line with SAMHSA methadone dosing guidelines, patients missing two or more consecutive days of treatment had their doses reduced (up to 50%) to ensure safe prescribing. Patients who miss 30 consecutive days of dosing (no-call/no-show) are administratively discharged and considered not retained. Urine toxicology is obtained monthly as standard-of-care per state regulations, is recorded in Methasoft, and includes tests for opiates, oxycodone, and fentanyl. In addition to treatment with medications, the clinic provides counseling, psychiatric, basic primary (wound) care, and social work and health home services. Most patients reside within one of five zip codes that immediately surround the clinic address, and present to the clinic either by referral or self-admission. Approximately 4-8 new patients are admitted into the methadone program per week.

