#### **5.0 RESEARCH DESIGN AND METHODS**

**5.1 Overview of study design.** We propose to conduct a proof of principle investigation to test the impact of a conditioned, open-label placebo intervention on methadone treatment outcomes. One-hundred twenty new intakes into methadone treatment for OUD will be approached, consented, and randomly assigned to one of two conditions: conditioned open-label placebo (group C-OLP) plus methadone or methadone/Treatment as Usual (TAU). We will follow them

for three months for a total of five in-person meetings (baseline, two weeks, and 1-, 2- and 3- months post-baseline). For the first two weeks, we will implement principles of pharmacological conditioning whereby placebo pills are temporally paired with the oral methadone hydrochloride solution that is provided to patients at the clinic (conditioning phase). Having established an association and contextualized the placebo as part of the therapeutic experience, placebos are then used as a dose extension pill (week 3 up to three months). Additionally, we are applying an open-label paradigm, giving participants information concerning the placebo pill in an honest and transparent manner. Our primary outcome is methadone dose three months after (baseline) entry into treatment; secondary outcomes include several measures of treatment success including comprehensive urine toxicology screens, self-reported drug use, and treatment retention. We are also capitalizing on this unique patient access opportunity to measure several personality and environmental factors associated with OUD, as well as factors associated with placebo response. A complete schedule of all study-related procedures is presented in Table 1.

| Table 1. Assessment timeline                 |                     |                            |             |                        |             |             |
|----------------------------------------------|---------------------|----------------------------|-------------|------------------------|-------------|-------------|
|                                              |                     | Phase I
(Weeks 1 and 2) |             | Phase II
(Weeks 3+) |             |             |
|                                              |                     | Meeting (Day Number)       |             |                        |             |             |

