### **7.3 Data analysis plan for secondary outcomes.**

**7.3.1 Treatment retention.** Chi-square analysis will be used to test group differences for the secondary outcome of treatment retention (continuous, up to 90 days).

**7.3.2 All other secondary outcomes.** Participants' self-reported days of drug use in the last 14 days was logged at each of the 5 total possible study visits. This information will be analyzed separately for opiates, cocaine, benzodiazepine, alcohol, and "other" drug use. For each variable, a mixed-effects longitudinal regression model will be fit to estimate and compare the mean number of days of reported drug use at each study visit by study group. The model follows:

$$\begin{aligned} \text{Expected}(\text{Numdays}_{ij}) = & \beta_0(\text{Baseline}_{ij}) + b_{0i} + \beta_{C\text{-OLP}2}(\text{C-OLP}2_{ij}) + \beta_{C\text{-OLP}3}(\text{C-OLP}3_{ij}) + \\ & \beta_{C\text{-OLP}4}(\text{C-OLP}4_{ij}) + \beta_{C\text{-OLP}5}(\text{C-OLP}5_{ij}) + \beta_{C\text{-OLP}2}(\text{TAU}2_{ij}) + \beta_{C\text{-OLP}3}(\text{TAU}3_{ij}) + \beta_{C\text{-OLP}4}(\text{TAU}4_{ij}) + \beta_{C\text{-OLP}5}(\text{TAU}5_{ij}) \end{aligned}$$

where

$\text{Numdays}_{ij}$  = Number of days of drug use for the  $i$ th person at the  $j$ th time point

$b_{0i}$  = Mean-0 normal random effect for subject  $i$ .

511 Baselineij = 1 if j=1, 0 otherwise.

512 C-OLP2ij = 1 if the patient is in the C-OLP group and time=2, 0 otherwise

513 TAU2ij = 1 if the patient is in the TAU group and time=2, 0 otherwise

514 and

515 remaining terms defined analogously.

516 By including a random effect for participant, the means are implicitly adjusted to account for  
517 differential dropout based on prior values of these variables. This model is fit using SAS proc  
518 mixed. At each time point, the hypothesis will be tested that the mean of the two groups differed.  
519 If we find that all the time-point means differed in the same direction, we would also perform a  
520 global (4 degrees of freedom) test of a difference between the groups at all four follow-up time  
521 points. For each drug analysis we will only include participants who used the drug at least once  
522 in the two weeks prior to baseline. All exploratory outcomes (OOWS, SOWS, Craving and  
523 WHO-QOL) will be analyzed in the same way as number of days of drug use, using the mixed  
524 effects longitudinal regression model.

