## **9.0 PROTECTION OF HUMAN SUBJECTS**

**9.1 Behavioral (instrument) data collected.** All behavioral assessment data will be collected with a facilitated self-report (i.e., a member of the study team will administer and fill in participant responses to the assessments) during each of the 5 meetings with participants. All administered assessments are described in an earlier section and in Table 1.

**9.2 Electronic Health Record Data Collected.** Consent will be obtained from each participant allowing for select information to be obtained. These data include: clinic attendance, clinic retention/discharge, and clinic urine drug screen test results at intake and monthly thereafter.

**9.3 Intervention:** Daily Placebo Pill Dispensing for Placebo Arm. Following treatment assignment on Day 0, the investigator will fill a placebo pill dispensing form indicating treatment assignment, and the patient will be walked to the methadone dosing station. Placebo pills will be stored and dispensed by the nursing staff of the UMATC. If the patient is assigned to the Placebo (C-OLP) arm, the investigator will observe the participant taking the placebo pill. In Phase 1 of the study (first two weeks), participants assigned to OLP will be given one pill, to be taken concurrently with the methadone. In Phase 2 (3 weeks up to 3 months), Placebo arm participants will continue to take the single (morning, or AM) pill, and will be given a second pill in a bottle as a take-home. They will be instructed to take this second pill twelve hours following the first pill, "at home, or wherever they may be." Participants will be asked to return the take-home pill bottle every day for refill. Circumstances may occur under which a participant may

need to be withdrawn from the protocol and include not following instructions given by team members.

**9.4 Materials: Placebo Pills.** The placebo (C-OLP) pill is produced by the University of Maryland School of Pharmacy Good Manufacturing Practice facility. The pills are composed of microcrystalline cellulose PH-102, magnesium stearate, and D&C Red 7 Ca Lake (inert chemicals and a food colorant, ingredients commonly contained in placebo pills manufactured by the pharmaceutical industry). Placebo pills are stored in a locked (Pxyis MedStation) medications cabinet maintained within the nurses' dosing window area.

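### Section 5.1 makes urine toxicology a secondary outcome, but 6.2, 6.3 and 7.3 leave it out, so the only drug-use comparison specified is self-report by participants who know their arm

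*Protocol*

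**What the plan says.** The Protocol describes its secondary outcomes in two places.

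- Section 5.1: "secondary outcomes include several measures of treatment success including comprehensive urine toxicology screens, self-reported drug use, and treatment retention". Urine is named separately from self-report.
- Section 6.2: "Secondary outcome measures include assessments of treatment retention, self-reported drug use, opioid withdrawal, craving, quality of life, and sleep". Urine is not named. The next sentence adds "All measures will be obtained via facilitated self-report at all five time points", with sleep as the only exception.

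Section 6.2.2 defines the drug-use measure: "Drug use is assessed via self-report of past-two-week use of four common substances", plus a fifth category for other drugs, scored as days used out of 14. Section 7.3.2, which covers all secondary outcomes other than retention, fits a mixed model to "compare the mean number of days of reported drug use at each study visit by study group" and treats OOWS, SOWS, craving and WHO-QOL the same way.

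Two urine sources are collected. Under 5.9, urine is taken at each of the five study visits and "the LC/MS/MS testing is conducted on all samples". The clinic also runs its own screens: "Urine toxicology is obtained monthly as standard-of-care per state regulations" (4.0). Section 9.2 gives the study access to "clinic urine drug screen test results at intake and monthly thereafter".

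**The concern.** A reader cannot tell from the Protocol whether urine toxicology is a secondary outcome. If 6.2 and 7.3 are followed, it is not one, and the drug-use comparison depends entirely on what participants say.

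Those answers are exposed to knowledge of the arm. The allocation is revealed to the participant on Day 0 (5.5), after a positively framed script on placebo effects (5.4.1, Appendix 1). A study team member asks the questions and fills in the responses (9.1). Section 5.8 states blinding for the dose-adjusting clinician, for the analysts, and for the study team during Day 0 procedures only. If participants in the conditioned open-label placebo arm (C-OLP) report somewhat fewer days of use because they know they take the pill, the 7.3.2 comparison can favour C-OLP with no true difference. An unsettled outcome list also leaves room to choose between urine and self-report once results are known.

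**Working it through.** **Step 1: does any section restore urine as an outcome?**

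| Section | Urine toxicology |
|---|---|
| 5.1 overview | Named as a secondary outcome |
| 5.9 procedures | LC-MS/MS on all five visit samples |
| 6.2 list | Not named |
| 6.2.1 to 6.2.7 | No entry |
| 6.3 other and exploratory outcomes | No entry |
| 7.3.1, 7.3.2 analyses | None |

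The conflict lies between 5.1 on one side and 6.2, 6.3 and 7.3 on the other.

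**Step 2: what could a reporting bias do?** The Protocol has no figure of its own on this point. Its power statement in 7.1 concerns dose escalation and is not involved.

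Inputs:
- 60 per arm, from 7.1.
- 30 per arm, assumed. Section 7.3.2 limits each drug analysis to participants who used that drug in the two weeks before baseline, so fewer than 60 may enter.
- SD of days used of 4, 5 or 6, assumed.
- Extra under-reporting in C-OLP of 1 day out of 14, assumed. No true difference.

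A two-sided 5% t-test at one visit stands in for the model's per-visit contrast. The noncentrality is ncp = shift / (SD × √(2/n)), and the chance of a significant result favouring C-OLP is the upper tail of the noncentral t with 2n − 2 degrees of freedom. For n = 60 and SD 4: ncp = 1 / (4 × √(2/60)) = 1.37.

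| n per arm | SD 4 | SD 5 | SD 6 |
|---|---|---|---|
| 60 | 27.4% | 19.1% | 14.6% |
| 30 | 15.7% | 11.5% | 9.3% |

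Without bias the figure is 2.5%. It moves a good deal with the assumed shift: at 60 per arm, 0.5 day gives 6.6% to 10.0% and 2 days gives 44% to 78%.

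**Step 3: what can urine show?** The inputs are 80% power, a two-sided 5% two-proportion test with pooled variance under the null, and TAU positivity of 50%, 60% or 70% (assumed).

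- One visit, 60 per arm: detectable differences are 24.5, 25.3 and 25.0 points.
- Average of four visits, within-person correlation 0.5 (assumed): effective n = 60 × 4 / (1 + 3 × 0.5) = 96 per arm, giving 19.7, 20.1 and 19.7 points.

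The 95% half-width for a difference is about 1.96 × √(2p(1 − p)/n). At p = 0.5 to 0.7 this is 17.9 to 16.4 points with n = 60, and 14.1 to 13.0 points with n = 96.

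One day out of 14 is 1/14 = 7% of the self-report scale. A positive or negative urine result does not count days, so the two scales cannot be matched directly, and intervals this wide could not show that a 1-day self-report difference was false.

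**The case against.** **The SAP may deal with urine.** The model, the positivity rule and the handling of missing samples can properly be left to an SAP, and their absence alone would not be a finding. But two Protocol sections disagree on which outcomes are secondary. Section 7.3.2 also writes its models out to the individual terms, so urine does not look deliberately deferred.

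**Both lists are worded as open.** This is true of 5.1 and 6.2 alike. The sentence after the 6.2 list, however, attributes all measures to self-report, which a urine assay cannot satisfy. That sentence is itself too broad: retention comes from clinic records (6.2.1) and OOWS is experimenter-administered (6.2.4). Those subsections correct it, so no analysis is harmed.

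**Open-label bias is inherent in the design.** This stands. Participants are meant to know their arm, and blinding the interviewers would remove only part of the problem. Urine collection at the same visits may also discourage under-reporting. An inherent bias is a reason to use the objective measure already in hand.

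**Stronger readings.** A reader might infer that the urine results would expose biased self-reports, or that the drug-use findings will be biased. The documents support neither. Step 3 shows that urine is too coarse for the first. For the second, both the shift and the SD are assumed. Nor does the text say that urine results will go unused; it gives them no defined place in the comparison.

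**Conclusion.** The point holds as a minor one. Section 5.1 conflicts with 6.2, 6.3 and 7.3 on whether urine toxicology is a secondary outcome, and under the later sections the only drug-use comparison specified is self-reported days. That comparison is open to reporting bias by design, while an objective measure collected at every study visit is left out of it.

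The conflict rests on the text alone. The size of any bias is unknown, and the 9% to 27% range is an illustration that depends on a 1-day shift, an SD of 4 to 6 days and 30 to 60 per arm. The primary outcome, dispensed methadone dose with adjustments made by a blinded clinician, is not affected.

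**What to change.** 1. **Outcome.** Add 6.2.8: LC-MS/MS positive for opioids other than methadone and its metabolite at Days 14, 28, 56 and 84, reported alongside self-reported days.
2. **Analysis.** In 7.3.2, compare the arms over the four follow-up visits with a repeated-measures logistic model containing arm, visit and arm by visit. Leave out a baseline-response term, because nearly all new intakes with moderate-to-severe OUD are likely to be positive at baseline (an assumption) and the term would be close to inestimable.
3. **Missing samples.** Do not count a missing sample as negative. Repeat the analysis with missing counted as positive.
4. **Clinic screens.** Report the monthly screens descriptively, as support. Section 5.9 places them at random monthly intervals, so they do not line up with the study visits.
5. **Wording.** Limit the facilitated self-report sentence in 6.2 to the questionnaires.

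If urine was never meant to be a secondary outcome, correct 5.1 instead. That removes the contradiction but leaves self-report as the only drug-use comparison. Either change should be made before results by arm are seen.

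The cost is one outcome definition and one model, with no new data. Urine shows presence and not days of use, and with 60 per arm it detects only about 20 to 25 points. It therefore complements self-report and cannot by itself confirm or rule out a small reporting bias.
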